As, to the best of our knowledge, this is the first study using a sequential design with two intensive meditation modalities, it is difficult to formulate specific hypotheses regarding the separate and combined effects of the MBSR and CCT programs on the selected outcomes. Thus, considering the two MBIs jointly, we expect that both programs will significantly: a) modify the DNA methylation and expression levels of specific genes and a reduction of the DNA methylation-based biological clock; b) reduce participants’ levels of psychological distress while increasing their levels of psychological functioning (i.e., mindfulness, compassion, emotion regulation, and well-being); c) change the EEG spectral profile of the resting state brain activity (i.e., changes in the balance between Alpha (8–14 Hz) and Theta (4–8 Hz) frequency bands and, regarding the organization of the brain functional networks, a modulation of the difference between the activation of the default mode network and the one corresponding to the salience network); d) alter awakening and bedtime cortisol levels leading to a steeper Diurnal Cortisol Slope (DCS); e) improve the efficacy of mood regulation following a negative mood induction (using an autobiographical memory task); f) reduce participants’ reactivity in an objective experimental stress test (i.e., Arithmetic Stress Test). In addition, given the multidisciplinary nature of the present project, we intend to provide a comprehensive view of potential changes in various areas of biological and psychological functioning and their interrelationships.

In general, we expect an overall pattern of results in which changes will be significantly higher for the combined effects of both MBIs than for each program separately. Moreover, based on previous literature comparing standard MBSR and CCT programs [24], we expect no major differences in primary outcomes between both programs, although the mechanisms of change may be different; in general, changes in MBSR will be mediated by cognitive variables (e.g., mindfulness) whereas changes in CCT will be mediated by socio-emotional variables (e.g., compassion). We also expect that the self-reported psychological changes associated with the MBIs will remain 3 months after the programs.

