## 2. Methods

### 2.1 Study design overview

We used the SPIRIT reporting guidelines. Participants will be randomly assigned to two groups starting with MBSR or CCT. A stratified randomization procedure, using the Research Randomizer Program (https://www.randomizer.org), performed by the principal investigator (CV), will be used to maintain the same percentage of male and female participants in each group. Participants from both groups will take part in a 7-day retreat, including training in both meditation-based practices. Participants will be blinded to group allocation starting with MBSR or CCT and will not receive any information of any kind about the study hypotheses. (IB and RZ will be in charge of participant recruitment and perform the randomization of each study group). Using a cross-over design, the participants will undergo their second training during the last three days of the retreat. Biological and psychological measures will be collected from both groups in the mornings of day 1 (before beginning the programs), day 4 (after the first program and before the beginning of the second program), and day 7 (at the end of the program). All psychological questionnaires will be administered online. Also, before going to bed, participants will be given a short questionnaire with eight questions about their general functioning during the day and their satisfaction with the progress of the program. Furthermore, a 3-month and a 12-month follow-up assessment will be conducted in both groups only for psychological questionnaires. (See Fig 1).

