The screening procedure will be conducted as follows: 1) First contact will be made through an online form expressing interest and commitment to participating in the study, where participants will be provided with some information on the retreat (date, location, and program characteristics) and will complete information on demographics, physical and psychological health history, and meditation experience. A waiting list will be formed for participants who did not sign up in time and wished to be considered in case a place became available. An expected final sample of 52 people will take part in the retreat being randomised to the MBSR training or CCT training for the first part of the retreat. All participants will complete the first arm of the study and then, after a half-day break, will be allocated to the opposite condition for the second study arm (following a cross-over design). There will not be a longer wash-out period due to the difficulties of extending the participants’ stay in the retreat for more days. However, in psychological studies with a cross-over design (e.g., [40]) there are usually no long periods between treatments. Moreover, introducing a wash-out period (days, weeks, or months) would introduce difficult-to-control confounders (e.g., different life events experienced by individuals) and would make comparability of treatments more difficult.

Participants will pay the cost of the retreat (i.e., meals and accommodation only) and will not receive any economic compensation for their contribution to the study. Participation requires informed consent, provided by the principal investigator (PI) or authorized full members of the research team, in which all the conditions of the study are reported. In case of any adverse effect, which is very unlikely in this type of intervention, participants may leave the study at any time without having to offer any explanation and without any kind of penalty. Furthermore, the team will facilitate any kind of help requested by participants during the retreat. The collection of biological information is innocuous, and blood and saliva samples will be collected by nursing professionals. Participants will be allowed to drop out at any point during the study as stated in the informed consent.

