### 2.4 Components and structure of the programs

Each program will comprise standard MBSR and CCT protocols in an intensive format to fit a retreat mode. Throughout the retreat, participants will be in silence, not talking to each other or using electronic devices. Each program will last 3 days in total, and all participants will go through both programs. On each retreat day, participants will spend a total of 4.25 hours of sitting meditation, 2 hours of walking meditation, 2 hours of explanations and discussing with the instructors, doubts or problems related to the practices, and 1 hour of mindful body movements (yoga/qigong). In total, participants will have 9 hours of practice each day. (A description of the contents of the programs is shown in Table 1).

**Table 1 pone.0283169.t001:** Description of the main practices of the retreat.

Practice	Description	Protocol	Day
**Basics of Mindfulness**	Practices and insights into mindfulness and acceptance. In this part, explanations are given on how to approach practices during the retreat, and how to deal with distractions, unpleasant bodily experiences, or difficult emotional states.	MBSR / CCT	1
**Yoga-Qigong**	Simple body exercises to relax tensions, unblock joint patterns, and develop mindfulness in movement. In the case of CTT, references are also made to self-care and self-compassion in movement.	MBSR / CCT	1
**Walking meditation**	The participant is trained in the ability to be aware while walking. The movement is slower than usual. Breathing and walking movements are integrated. In the MBSR protocol, awareness of the breath and the body is encouraged. In CCT, loving-kindness or compassion is developed while walking.	MBSR / CCT	2
**Body Scan**	Attention is brought to the various parts of the body. From the soles of the feet to the top of the head. The aim is to develop mindfulness. Every time there is a distraction, the attention is gently taken up again on the sensations of the body.	MBSR	1
**Awareness of Breathing**	Attention is focused on breathing. Two options are given, depending on the preference of the participants (i.e., focusing attention on the tactile sensations of air in the nostrils or on the sensation of the movement of the abdomen).	MBSR	2
**Awareness of Thoughts**	It aims to focus attention on the activity of the mind (i.e., on the spontaneous generation of thoughts and emotions).	MBSR	3

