However, we recognize that the protocol has some limitations. Participants in mindfulness studies are typically self-selected, which is a difficult problem to control in research on meditation procedures. Although the cross-over design will allow us to answer important research questions (e.g., the existence of additive effects of the two modalities), it is not certain that the results can be easily transferable to other settings. Also, the retreats include compact and intensive training that is offered in a short period of time, lacking homework exercises. However, although more time may be required to produce lasting psychobiological changes, previous studies support the idea that brief retreat interventions can detect change [35, 76]. Even in an 8-hour intensive mindfulness-based retreat, significant transcriptional [36] as well as DNA methylation changes were observed in blood samples, and affected in genes related to important cellular pathways (such as fatty acid metabolism, DNA repair, and chromatin remodeling, among others) [35]. Furthermore, differentially methylated CpGs were enriched in binding sites of particular transcription factors, involved in immune response and inflammation [35]. These findings suggest that the changes observed are not random, and seem to be induced by the meditation practice, even after only one day of intervention.

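### Combined versus single-program benefit cannot be identified: both programs are seen only on Day 7 after six retreat days, one program only on Day 4 after three, and nobody continues a single program

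*Protocol article*

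**What the plan says.** The Introduction (section 1) expects that "changes will be significantly higher for the combined effects of both MBIs than for each program separately". It also gives the evaluation of additive effects as a reason for the sequential approach. The Discussion (section 3) says that "the cross-over design will allow us to answer important research questions (e.g., the existence of additive effects of the two modalities" can be settled, with additivity as its example.

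The design is set out in three places:

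- **Section 2.1:** "Participants will be randomly assigned to two groups starting with MBSR or CCT". Measurements during the retreat fall on day 1, then "day 4 (after the first program and before the beginning of the second program), and day 7 (at the end of the program".
- **Section 2.2:** "All participants will complete the first arm of the study and then, after a half-day break, will be allocated to the opposite condition". It adds that "There will not be a longer wash-out period".
- **Section 2.4:** "Each program will last 3 days in total, and all participants will go through both programs", and "In total, participants will have 9 hours of practice each day".

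Section 2.7 plans an Order by Time repeated-measures ANOVA, with three time points for the biological measures and the memory task and four for self-report, followed by corrected post-hoc comparisons. The Discussion concedes that silence, rest and other retreat conditions may contribute to change, but does not connect this with the combined-versus-single hypothesis.

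**The concern.** Comparing both programs with one program needs people who differ in that respect and are otherwise alike. Here the two states occur at different times in the same people, in both sequences. Whoever has had both programs has also had twice the practice, twice the days in silence and in a controlled setting, and one more round of assessments. Table 1 adds to this: basics of mindfulness, yoga-qigong and walking meditation belong to both protocols, so the second block also gives more of what was already received.

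A larger change on Day 7 than on Day 4 could therefore be read as a benefit of joining mindfulness to compassion training when three more days of the same program could have given the same pattern. That reading bears on one of the trial's stated hypotheses and on a stated reason for the design.

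**Working it through.** **1. Dose at each assessment** (section 2.4). Day 4: 3 days × 9 h = 27 h, one program. Day 7: 6 days × 9 h = 54 h, both programs. This holds in both sequences.

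**2. What the cell means can identify.** Let μ be the Day 1 mean, τ4 and τ7 the generic change by Day 4 and Day 7 (time, dose, retreat conditions, repeat testing), δ the MBSR minus CCT difference after one program, and γ the effect of having had both.

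| Sequence | Day 1 | Day 4 | Day 7 |
|---|---|---|---|
| MBSR first | μ | μ + τ4 + δ/2 | μ + τ7 + γ |
| CCT first | μ | μ + τ4 − δ/2 | μ + τ7 + γ |

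The difference between groups on Day 4 is δ, so δ is estimable. γ appears only in the sum τ7 + γ. The design matrix has 5 columns and rank 4, and γ is not estimable. An order term of ±ω/2 on Day 7 changes nothing, because it cancels from the average of the two sequences and leaves τ7 + γ as before. In the planned ANOVA the alias sits in the Time effect; Order and Order by Time concern program, order and carry-over differences.

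The contrast that can be estimated is (τ7 − τ4) + γ, which is six retreat days with both programs against three days with one.

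**3. What would identify γ.** Two continuation arms (MBSR throughout, CCT throughout) would have Day 7 means of μ + τ7 ± δ/2. The rank becomes 5 of 5 and γ is estimable, provided that three further days have the same effect in either program. More people in the two existing sequences leave the rank at 4.

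**4. Illustration of size.** The documents give neither a gain per three-day block nor a correlation between assessments, so both are assumed. Set γ = 0 and let each block add a generic gain g in SD units. For correlation r between Day 4 and Day 7, the standardised paired difference is dz = g / √(2(1 − r)). The probability of significance comes from the noncentral t with n − 1 degrees of freedom and noncentrality dz√n. All 52 people of section 2.3, two-sided 5%, uncorrected:

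| r | g = .185: dz | significant | g = .37: dz | significant |
|---|---|---|---|---|
| .3 | .156 | 20% | .313 | 60% |
| .5 | .185 | 26% | .370 | 74% |
| .7 | .239 | 39% | .478 | 92% |
| .8 | .293 | 54% | .585 | 99% |

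The figure .37 is borrowed from section 2.3, which takes it from well-being outcomes in mindfulness retreats and does not say whether it is a d or an f. Half of it, .185, is what a linear gain would give per block if .37 described the whole retreat.

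The probabilities fall under other choices. For g = .37 and r = .5:

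- n = 42 (before the allowance for dropout): 65%.
- n = 52 with Bonferroni over three pairwise comparisons: 58%.
- n = 52 with Bonferroni over six pairwise comparisons (four time points): 48%.
- One sequence of 26, uncorrected: 44%.
- One sequence of 26, with Bonferroni over three: 27%.

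**The case against.** The best defence is pragmatic. Two complete programs take longer than one, so extra contact time is part of what is delivered, and the change from three days with one program to six days with both can be estimated within person. That stands, and it is why the contrast should be reworded and kept. It does not support the word additive, or an advantage of combining.

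The authors are also cautious in places. The Introduction calls specific hypotheses on separate and combined effects hard to formulate, and the Discussion admits retreat influences. Repeat testing is partly reduced in the two stress tasks (section 2.5.2), because the numbers and the memories differ from day to day. These points soften the concern. They do not remove the alias, and the Discussion still says that additivity can be answered.

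Four stronger conclusions might be inferred, and the documents support none of them:

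- *That three more days of one program would give the same result.* No dose-response is given, and a plateau is equally possible. The right word is could.
- *That a spurious finding has a known probability, such as 74%.* That is one cell of an assumed table; the range is wide.
- *That the authors would present a larger Day 7 change as proof of a combined benefit.* Nothing in the text shows this.
- *That the design answers only two randomised questions.* The difference between sequences in Day 4 to Day 7 change is also a randomised contrast, informative on MBSR versus CCT if there is no differential carry-over. Order can also be compared at follow-up for self-report.

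**Conclusion.** The concern holds as a matter of identification. With two switching sequences, both programs against one is the same comparison as Day 7 against Day 4, so the combined-versus-single hypothesis and the additive-effects claim ascribe to the design a property that it lacks. This follows from the layout alone and is true at any effect size and any sample size.

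The percentages only show that the matter is not academic. They assume no combination effect, an equal generic gain in each block, an uncorrected paired test and all 52 people with data. Under those assumptions Day 7 against Day 4 is significant in about 20-54% of trials (.185 SD) or 60-99% (.37 SD).

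The short break adds a second limit: change from Day 4 to Day 7 may include carry-over from the first program, so it is not the second program's own effect either.

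**What to change.** - **Introduction, hypothesis.** Restate it as a cumulative package contrast: change after six retreat days with both programs compared with change after three days with one.
- **Introduction and Discussion, additive effects.** Remove the claim, or qualify it by saying that the design does not separate combination from dose and retreat time.
- **Limitations.** State that Day 4 to Day 7 change cannot be attributed to combining the programs or, given only a half-day break, to the second program alone.
- **MBSR versus CCT.** Rest it on the randomised between-group contrast on Day 4. Use the difference between sequences in Day 4 to Day 7 change only as support, under a stated assumption of no differential carry-over.
- **Order.** Rest it on the between-group contrast on Day 7 and, for self-report, at the 3- and 12-month follow-ups.

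The cost is wording in the hypotheses, analysis section and limitations. Data collection is unchanged; the trial gives up a claim that its design cannot support. Continuation arms would make the combination effect estimable, but they belong to a different and much larger trial. For a standardised difference of .37 on Day 7 (two-sided 5%, no baseline adjustment), about 115 people per pooled side would be needed for 80% power, and 52 people split 26 against 26 would have about 27%.

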## 2. Methods

### 2.1 Study design overview

We used the SPIRIT reporting guidelines. Participants will be randomly assigned to two groups starting with MBSR or CCT. A stratified randomization procedure, using the Research Randomizer Program (https://www.randomizer.org), performed by the principal investigator (CV), will be used to maintain the same percentage of male and female participants in each group. Participants from both groups will take part in a 7-day retreat, including training in both meditation-based practices. Participants will be blinded to group allocation starting with MBSR or CCT and will not receive any information of any kind about the study hypotheses. (IB and RZ will be in charge of participant recruitment and perform the randomization of each study group). Using a cross-over design, the participants will undergo their second training during the last three days of the retreat. Biological and psychological measures will be collected from both groups in the mornings of day 1 (before beginning the programs), day 4 (after the first program and before the beginning of the second program), and day 7 (at the end of the program). All psychological questionnaires will be administered online. Also, before going to bed, participants will be given a short questionnaire with eight questions about their general functioning during the day and their satisfaction with the progress of the program. Furthermore, a 3-month and a 12-month follow-up assessment will be conducted in both groups only for psychological questionnaires. (See Fig 1).

**Fig 1 pone.0283169.g001:**
[figure not shown]
Cross-over design.

### 2.2 Participants: Recruitment and selection

Individuals from the general population will be recruited through the Nirakara-Lab website, a university-associated research center specializing in Mindfulness and Compassion-Based programs for the general population. Participants will be invited to join the study on the university’s official website offering the MBSR and CCT programs (www.nirakara.com). This is a widely known national website for the general public interested in research and training in meditation. An e-mail will be sent to the thousands of individuals registered in the website newsletter. In any case, participation in the study will be open to any interested individual who meets the inclusion and exclusion conditions. To control for potential self-selection biases, which is a common shortcoming of MBIs research [37–39], there will be statistical controls on key issues such as years and type of previous meditation practice, if any, sociodemographic information, and mental health status. Individuals interested in participating in the retreat will be interviewed by members of the research team (RZ and CA) to screen their suitability for the study. Inclusion criteria will be being a healthy adult between 25 and 65 years old who is interested in meditation and compassion techniques to regulate their mood and stress. Exclusion criteria include having a current or past self-reported diagnosable serious or disabling mental disorder (in particular, PTSD, major depression, psychotic disorders, and/ or use of alcohol or drugs disorders) or having a current or past (i.e., less than 5 years ago) medical or physical condition that may affect the immune system (i.e., autoimmune disease, chronic severe infections, HIV, cancer), pregnancy, serious chronic illnesses, as well as the consumption of psychotropic drugs. Individuals with current habits (i.e., smoking, alcoholism, substance abuse) or taking specific medications (e.g., corticoids) that might affect the immune system are also excluded. Also, individuals planning to travel from a different time zone or long-travel times will be excluded as that might affect the immune system.

The screening procedure will be conducted as follows: 1) First contact will be made through an online form expressing interest and commitment to participating in the study, where participants will be provided with some information on the retreat (date, location, and program characteristics) and will complete information on demographics, physical and psychological health history, and meditation experience. A waiting list will be formed for participants who did not sign up in time and wished to be considered in case a place became available. An expected final sample of 52 people will take part in the retreat being randomised to the MBSR training or CCT training for the first part of the retreat. All participants will complete the first arm of the study and then, after a half-day break, will be allocated to the opposite condition for the second study arm (following a cross-over design). There will not be a longer wash-out period due to the difficulties of extending the participants’ stay in the retreat for more days. However, in psychological studies with a cross-over design (e.g., [40]) there are usually no long periods between treatments. Moreover, introducing a wash-out period (days, weeks, or months) would introduce difficult-to-control confounders (e.g., different life events experienced by individuals) and would make comparability of treatments more difficult.

Participants will pay the cost of the retreat (i.e., meals and accommodation only) and will not receive any economic compensation for their contribution to the study. Participation requires informed consent, provided by the principal investigator (PI) or authorized full members of the research team, in which all the conditions of the study are reported. In case of any adverse effect, which is very unlikely in this type of intervention, participants may leave the study at any time without having to offer any explanation and without any kind of penalty. Furthermore, the team will facilitate any kind of help requested by participants during the retreat. The collection of biological information is innocuous, and blood and saliva samples will be collected by nursing professionals. Participants will be allowed to drop out at any point during the study as stated in the informed consent.

The study has been approved by the University Ethics Committee (Ref. 22/449-E, July 2022) and has been pre-registered (clinicaltrials.gov, Identifier: #NCT (NCT05516355). Any modification to the protocol will be reported both to the Ethics Committee and the trial registration site. Participants will be informed in advance of the results of the study to be published in scientific journals.

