** *Psychological measures (outcomes of programs)* **					
• Perceived Stress Scale	x				
• Depression Anxiety Stress Scales (DASS-21)		x	x	x	x
• Patient Health Questionnaire (PHQ-15)	x			x	x
• Patient Health Questionnaire (PHQ-9)	x			x	x
• Satisfaction with Life Scale (SWLS)	x			x	x
• State Difficulties in Emotion Regulation (S-DERS-21)		x	x	x	x
• State Mindfulness Scale (SMS)		x	x	x	x
• State Self-Compassion Scale (SSCS)		x	x	x	x
• Fear of Compassion (FOC)		x	x	x	x
• Hedonic and Arousal Affect Scale (HAAS)		x	x	x	x
• Meditation-Related Adverse Effects Scale			x	x	x

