#### 2.5.2 Psychological measures

*a) Self-report measures*. Most of these measures were developed in studies with the general population and have been also used in previous MBI studies in healthy individuals [22]. They have shown good or excellent psychometric properties and cover selected psychological distress and functioning constructs (i.e., stress, anxiety, depression, mindfulness, compassion, well-being, and emotion regulation) and all will be administered online via Qualtrics with individualized links (Table 2):

*Psychological distress*. Depression Anxiety Stress Scales (DASS-21) [44, 45].*Psychological well-being*. Satisfaction with Life Scale (SWLS) [46, 47].*Mindfulness*. State Mindfulness Scale (SMS) [48].*Anxiety*. State-Trait Anxiety Inventory (STAI-20) [49, 50].*Somatic Symptoms*. Patient Health Questionnaire (PHQ-15) [51, 52].*Sleep difficulties*. DSM-5 sleep difficulties [53].*Compassion*. State self-compassion State Self-compassion Scale (SSCS) [54, 55].*Fear of Compassion*. The Yourself subscale from the Fear of Compassion Scale [56].*Emotion Regulation*. State Difficulties in Emotion Regulation (S-DERS-21) [57, 58].*Current mood*. Positive and Negative Affect Schedules (PANAS) [59, 60].*Daily assessments of psychological functioning*. A 7-item scale to assess participants’ average state of mindfulness, mind wandering, compassion to others, self-compassion, well-being, the richness of life, and utility of the contents of the program every day.*Affect in the last 3 days*. Hedonic and Arousal Affect Scale (HAAS) [61].*Meditation Adverse Effects*. Meditation-Related Adverse Effects Scale–Mindfulness-Based Program (MRAESMBP) [62].*Program satisfaction*. Client Satisfaction Questionnaire (CSQ-8) [63, 64].

*b) Psychological stress tasks*. ***b*.*1) Stress Reactivity*.** Arithmetic Stress Test: a standardized laboratory stress induction procedure, that is part of the Trier Social Stress Test [65, 66], will be used to assess participants’ stress reactivity. Individuals are asked to repeatedly subtract a given 2-digit number (i.e., 13) from a 4-digit number (e.g., 1022). These numbers were changed for each of the three assessment days. Participants are asked to write their responses on a personal computer as quickly as possible. Time is limited to 3 minutes to increase the stressful nature of the task. Pre-post stress level changes in mood will be assessed with the PANAS and STAI.

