Intention-to-treat (ITT) analyses will be conducted with all participants, regardless of session or outcome measure completion. The pattern and percentage of missing data will be explored before analysing the data. It should be noted that the chances of missing data will be minimized because the questionnaire administration format via Qualtrics does not allow progress to be made until all items in each questionnaire are completed. Binary logistic regression will be used to evaluate the assumption that data is Missing at Random (MAR). ITT mixed models (restricted maximum likelihood (REML) estimation) will be used to account for missing data MAR. If missing were not random (MNAR), we would conduct Multiple Imputation and Pattern Mixture Models incorporating the predictor responsible for the missingness into the model. In any case, sensitivity analysis will be performed, comparing the main outcomes between completers and imputed values. To safeguard the confidentiality of participants’ data, all samples will be anonymized with alpha-numeric codes. These codes will not carry any personal information. Personal data linked to the alpha-numeric code will not be included in any files used for data analyses and will remain separate from the main database. Data displayed in public repositories (e.g., GitHub or datadryad.org), linked to the resulting publications, will always be anonymized. Data supporting each published study will be included within the article and/or supporting materials. To improve blinding integrity [72], personnel who will analyse the data collected from the study are not aware of the treatment applied to any given group. The authors will be fully responsible for handling and analyzing data independently from any sponsor. All the questionnaires included in the protocol as well as a copy of the informed consent, are available at https://osf.io/gczas/?view_only=7864451a24cf4a82824f6f298b1bbf0f.

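### The only adverse-effects measure described is a scheduled self-report scale, while an affected participant may leave the study without explanation; unless leavers are also asked, harms may be under-counted

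*Protocol article*

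**What the plan says.** Section 2.2 deals with adverse effects in one sentence: "In case of any adverse effect, which is very unlikely in this type of intervention, participants may leave the study at any time", and it continues "without having to offer any explanation and without any kind of penalty". What may be left is the study, not only the retreat. The next sentence adds that "the team will facilitate any kind of help requested by participants during the retreat". The same section ends with a general right that is not tied to harm: "Participants will be allowed to drop out at any point during the study as stated in the informed consent".

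Section 2.5.2 names one adverse-effects instrument, a self-report scale. In Table 2 the row "Meditation-Related Adverse Effects Scale" is marked under Day 4, Day 7 and the 3- and 12-month follow-up, and nowhere else. Section 2.5.2 also says that the self-report measures are completed online through individual links.

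Section 2.1 adds a bedtime "short questionnaire with eight questions about their general functioning during the day" and satisfaction with the program. Section 2.5.2 describes a 7-item daily scale and lists its content: mindfulness, mind wandering, compassion to others, self-compassion, well-being, richness of life and utility of the program. None of the listed items asks about adverse effects.

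Section 2.7 says: "Intention-to-treat (ITT) analyses will be conducted with all participants, regardless of session or outcome measure completion". It plans REML mixed models for data missing at random. For data missing not at random it plans multiple imputation and pattern mixture models that use the predictor of missingness. It does not mention adverse effects.

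**The concern.** Set together, the two stated elements can lose the cases that matter most for a harm count. The first scheduled use of the scale is Day 4. A participant who becomes distressed on Day 2 and takes up the option in 2.2 is gone before that, and need not say why. Nothing in the article links such a departure to an adverse-effect record. The harm measure can then be missing because of the harm.

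If that happened, the reported frequency would describe mainly those who tolerated the retreat, and it would tend to agree with the prior statement in 2.2 that adverse effects are very unlikely. Any comparison of harms between the two order groups at Day 4 could also favour a first program that people had left, although the article does not specify such a comparison. The participants are healthy volunteers, and the Discussion hopes to inform preventive use in the wider community, so a credible harm count matters. Information not collected at departure may not be recoverable at the analysis stage.

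**Working it through.** **Figures in the article.** It gives no adverse-effect rate, so there is no harm figure to reproduce. The only figure on loss is the 20% allowance in 2.3: 21 × 1.2 = 25.2, rounded up to 26 per group, or 52 in total. This reproduces. By its own description it covers pre-registered people who drop out at the last minute and incomplete data at collection or analysis. It is not an estimate of how many people leave the retreat, and is not used as one here.

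**Inputs for an illustration.** None of these three is in the article; all are assumed.
- p: true share with an adverse effect, range 5% to 30%.
- q: share of affected people who leave before answering the scale, 0 to 100%.
- w: share of unaffected people who leave before answering, 0 to 10%.

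**Rate among those still answering**, if leavers are not asked: p(1−q) / [p(1−q) + (1−p)(1−w)].

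| p | q | w | Calculation | Rate seen |
|---|---|---|---|---|
| 10% | 0 | 0 | 0.100 / (0.100 + 0.900) | 10.0% |
| 10% | 10% | 10% | 0.090 / (0.090 + 0.810) | 10.0% |
| 10% | 25% | 5% | 0.075 / (0.075 + 0.855) | 8.1% |
| 10% | 50% | 5% | 0.050 / (0.050 + 0.855) | 5.5% |
| 10% | 100% | 0 | 0 / (0 + 0.900) | 0% |
| 10% | 5% | 10% | 0.095 / (0.095 + 0.810) | 10.5% |
| 5% | 50% | 5% | 0.0250 / (0.0250 + 0.9025) | 2.7% |
| 20% | 50% | 5% | 0.100 / (0.100 + 0.760) | 11.6% |
| 30% | 50% | 5% | 0.150 / (0.150 + 0.665) | 18.4% |

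The rate is too low when q > w, correct when q = w, and slightly too high when q < w.

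**If leavers stay in the denominator as non-events**, the rate is p(1−q), which is low whenever any affected person leaves. With p = 10% and q = 50% it is 0.10 × 0.50 = 5.0%.

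**What bounds would show.** Suppose 5 of the 52 report an adverse effect and some others leave without a known reason.
- 3 unexplained leavers: 5/49 = 10.2% among those remaining. Over all 52, the bounds are 5/52 = 9.6% (no leaver had an event) to 8/52 = 15.4% (all did).
- 5 unexplained leavers: 5/47 = 10.6% among those remaining. The bounds are 5/52 = 9.6% to 10/52 = 19.2%.

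In a trial of this size, a handful of unexplained departures changes what can be said about harm.

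**Whether 2.7 covers the gap.** Analysing all participants does not supply a value that was not collected. The planned methods for data missing not at random need the predictor of missingness, and an unexplained departure records none.

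**The case against.** The strongest reply is that this is a condensed article. Procedures for withdrawal and for collecting adverse events commonly sit in the full protocol and the consent form, and 2.2 refers to the consent form for drop-out. This stands: the absence of such a procedure here is no finding. What remains is that the article does state a schedule for its one adverse-effects measure and does state what an affected participant may do, and the two together leave a gap.

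Four stronger readings are tempting, and the document supports none of them.
- A reader might infer that leavers are denied the scale. Table 2 says when it is given, not who is excluded. The questionnaires are online and follow-up is planned in both groups. The article is silent on whether leavers receive them.
- A reader might infer that leaving is the plan's response to harm. It is a voluntary right, and help on request is offered beside it. Not having to explain does not prevent staff from inviting a reason.
- A reader might state as fact that the harm rate is biased toward zero. Among those still answering, this needs affected people to leave more often than others. With equal rates, or with no departures, there is no bias.
- A reader might take the difference between 52 and 42 in 2.3 as ten people leaving the retreat, and build a harm rate on it. The allowance is for other losses.

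It is also fair to say that an all-participants analysis does not require every value to be observed, and that the bedtime ratings give some data up to departure. Those ratings concern functioning and satisfaction, however, and the seven listed items do not record adverse effects. Section 2.1 counts eight questions, and the eighth is not identified.

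**Conclusion.** The point holds in conditional form. As described, adverse effects are captured only by a self-report scale at Day 4, Day 7 and the two follow-ups, and an affected participant may leave the study unexplained. Under-counting is likely if two conditions are met: leavers are not also asked, and affected people leave more often than unaffected people. The second is plausible, because 2.2 itself mentions leaving in connection with adverse effects, but the article gives no data on it.

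The size cannot be derived from the document. The percentages shown are illustrations under assumed values and should not be read as estimates for this trial. The case for acting rests on the low cost of the change and on the fact that what is not collected at departure cannot be restored by the analysis.

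**What to change.** In 2.2, distinguish stopping the retreat from withdrawing from the study. Invite anyone who stops to complete the existing online adverse-effects scale at departure and to give a reason if willing. Send the 3- and 12-month online questionnaires to everyone who stops, unless consent to follow-up is withdrawn. If the full protocol or consent form already provides for this, a sentence in 2.2 saying so is enough.

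In 2.7, state that adverse effects are reported as numbers over all randomised, by order group. List departures without a known reason, and show the rate twice: with these counted as events and as non-events.

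The cost is a change of protocol and consent wording, one further use of existing online links, and a few minutes for each person who leaves. The harm rate may look less favourable. The right to leave without explanation and without penalty is kept.
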